## Implications of the hypothesis

SATURN project is a European multicentre study that aims to provide an in-depth knowledge of ARB acquisition through the analysis of antibiotic classes, duration of treatment and dosage in the nosocomial setting by a multidisciplinary approach. The SATURN project website http://www.saturn-project.eu provides the information and details concerning the different WPs and the entire project.

Several outcomes will be obtained at the end of the study (December 2014, expected): the rate of acquisition of target ARB by 1,000 antibiotic-days according to different classes of antibiotics, duration of therapy, and antibiotic combinations (monotherapy versus combinations); risk factors associated with new colonisation by target ARB; and risks for nosocomial infections due to target ARB after a cycle of antibiotic therapy adjusted by length of hospitalisation and ward colonisation pressure.

The WP4 study is currently recruiting patients in all clinical centers. The accomplishment of the study will be pursued thanks to the great strive of all clinicians, nurses and microbiology staff in every study step. An advertising campaign (posters, stickers and pictures) was performed in the selected wards in order to thrill and sensitise the recruited staff.

The results of the study should lead to the design of specific infection control measures for preventing spread of ARB in hospitalised non-ICU patients undergoing antibiotic therapy. A potential benefit for selective screening in high-risk patients during antibiotic therapy or shorter duration of antibiotics in such patients might be hypothesised. Readily available colonisation information could impact empiric therapy for nosocomial infections or, for example, the potential need of mupirocin prophylaxis for patients colonised by MRSA during hospitalisation. Assessment of the usefulness of the recommendations derived from the results of the SATURN study should be of valuable help for those in charge of infection control, for hospital administrators, and for those managing budgets of large healthcare organisations.

We do expect that SATURN project results will have a direct impact on clinical practice, improving the appropriateness of antibiotic prescribing policy, the prevention of antibiotic-resistant infections and the heightener of patients' quality care.

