## Testing the hypothesis

All adult patients (> 18 years) starting intravenous and/or oral antibiotic treatments during hospitalisation will be included in the study. Written informed consent will be obtained by every patient before study inclusion. Exclusion criteria will be pregnancy and recent nose surgery. Patients starting antibiotic therapy *per os *and/or intravenously will be sampled at antibiotic start (t_0_, within one hour) and at the following intervals: day 3 (t_1_), 7 (t_2_), 15 (t_3_), 30 (t_4_) (Figure 1). Patients colonised with MRSA and/or extended-spectrum β-lactamase (ESBL)-producing gram-negative bacteria before starting antibiotic therapy (t_0 _sample) will be excluded from follow-up cultures and analysis. Patients will be followed during the hospitalisation and afterwards for a total of 30-day from the inclusion in the study. Screening will be performed in outpatient clinics after patients' discharge from the hospital, if possible.

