### Variables

The following variables will be identified in cases and controls: age; gender; reason for admission; inter and intra-wards transfers; admission from home or other acute or long-term care institutions; previous hospitalisation; surgical procedures; Intensive Care Unit (ICU) stay (previous 12 months); residency in long-term care facility; transfer form another hospital; nursing and/or medical domiciliary assistance; urinary catheter; central venous catheter (CVC, at hospital admission); underlying conditions (Infectious Disease-specific Chronic Disease Score, CDS-ID); room sharing with a ESBL or MRSA patient; previous MRSA or ESBL carrier; consciousness at admission; antibiotic therapy (previous 30 days).

Antibiotic therapy will be reported as for daily dosage, frequency of dosage(s), route of administration, type of antibiotic(s), reason for starting and stopping, duration of therapy. At every clinical follow-up the following variables will be also detected: presence of urinary catheters; CVC; surgery; room sharing with a ESBL or MRSA positive patient; MRSA or ESBL-producing gram-negative infections (including type of infection, therapy, and outcome); albumin, creatinine and blood urea nitrogen levels.

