### Statistical analysis

The assessable population for each target organism will include all treated patients from whom baseline screening and at least one follow-up screening will be available. The incidence of colonisation will be defined by the number of new cases of colonisation for 1,000 days of antibiotic therapy. Only patients with a negative baseline (t_0_) will be included in the longitudinal analysis. The length of exposure to antibiotic therapy for patients newly colonised by ARB will be defined by the number of days between the inclusion in the study and the date of the first positive sample. The length of exposure to antibiotic therapy for patients not colonised will be defined by the number of days between the inclusion in the study and the date of antibiotic discontinuation. The colonisation pressure will be calculated for each center and defined as the average point of prevalence for antibiotic-resistant bacteria for all days until acquisition or discharge. Time-to-event analysis (in days) between the inclusion in the study and the acquisition of colonisation will be done using Kaplan-Meier curves and Cox proportional hazard regression modeling in which the number of days until acquisition will be the dependent variable. Two nested case-control studies will be performed:

#### Case control study 1

To define the impact of antibiotics on new acquisition of MRSA and ESBL-producing *Enterobacteriaceae*, a matched case-control study will be done (ratio 1:4). The control group will be selected among patients not receiving antibiotics, admitted in the same ward on the day of the corresponding case, with negative cultures at hospital admission. Matching criteria will include: age (± 5 years), sex, and total length of hospitalisation.

#### Case control study 2

To define individual level of risk related to specific antibiotics, patients acquiring MRSA and ESBL-producing *Enterobacteriaceae *will be compared with patients not acquiring ARB after starting antibiotic therapy (ratio 1:4). Previously known risk factors or clinically relevant significant variables from the univariate analysis will be considered for inclusion in multivariate logistic regression analysis. The Hosmer and Lemeshow goodness-of-fit test will be used to assess model fit.

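### The promised acquisition rate by duration of therapy has no named grouping variable, and the only exposure length defined for analysis is set by the outcome, so either natural reading can give a spurious duration effect

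*Protocol article*

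**What the plan says.** All references are to the protocol article.

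- **Promised result** (Implications of the hypothesis): "the rate of acquisition of target ARB by 1,000 antibiotic-days according to different classes of antibiotics, duration of therapy, and antibiotic combinations". Neither the duration bands nor the variable that assigns patients to them is given. The same section looks ahead to duration as a practical message: "shorter duration of antibiotics in such patients might be hypothesised".
- **Rate** (Statistical analysis): "The incidence of colonisation will be defined by the number of new cases of colonisation for 1,000 days of antibiotic therapy".
- **Exposure length** (Statistical analysis): for newly colonised patients, "the number of days between the inclusion in the study and the date of the first positive sample"; for the others, "the number of days between the inclusion in the study and the date of antibiotic discontinuation".
- **Recorded treatment data** (Variables): "type of antibiotic(s), reason for starting and stopping, duration of therapy". Course length is therefore collected as an item of its own.
- **Follow-up** (Testing the hypothesis): "Patients will be followed during the hospitalisation and afterwards for a total of 30-day from the inclusion in the study", with swabs on days 3, 7, 15 and 30. A first positive can therefore fall after treatment has stopped.

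**The concern.** A rate by duration is interpretable only if the outcome does not choose the duration band and if events and days cover the same period. The stated exposure length meets neither condition.

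A patient on a 14-day course who is positive on day 3 counts as 3 days of exposure. A patient on a 5-day course who is first positive on day 30 counts as 30 days. If these lengths assign the bands, the outcome decides the band.

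If recorded course length assigns the bands, that problem goes, but the counting rule stays. Positives up to day 30 enter the numerator, while non-acquirers' days end at discontinuation. Short courses then carry few days against the same 30-day opportunity to turn positive.

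At stake is a named output of the study. A larger sample would not remove the bias; it would only estimate it more precisely.

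**Working it through.** The plan gives no rate by duration to reproduce. The only plan figures used are the swab days and the 5% acquisition proportion from Sample size. Course lengths and bands are **assumptions**. In every scenario course length has no effect on acquisition.

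**1. Banding by exposure length, clean on-therapy clock.** Assume a constant hazard of 5 per 1,000 days and courses uniform over 3 to 14 whole days. Exposure is L = min(acquisition day, course), and rate = 1,000 × events / sum of L. Per 1,000 patients:

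- L of 7 days or less: 30.3 events / 2,140 days = 14.2
- L of 8 to 14 days: 11.1 events / 6,174 days = 1.8

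The ratio is about 8; the true ratio is 1. It stays about 8 at hazards of 2 and 10 per 1,000.

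**2. Banding by exposure length, clock as written.** Assume 5% acquire, evenly over 30 days, and courses of 5, 7, 10 and 14 days in 25/35/25/15% of patients. Per 1,000 patients there are 50 acquirers. Their first positives fall on day 3 (5.0), day 7 (6.67), day 15 (13.33) and day 30 (25.0).

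- 7 days or less: events 5 + 6.67 = 11.67; days 5×3 + 6.67×7 + 237.5×5 + 332.5×7 = 3,577; rate 3.3
- 8 to 14 days: no swab falls here, so 0 events; days 237.5×10 + 142.5×14 = 4,370; rate 0
- 15 days or more: events 13.33 + 25 = 38.33; days 13.33×15 + 25×30 = 950; rate 40

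No assumed course exceeds 14 days, so the last band contains acquirers only.

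**3. Banding by recorded course, counting as written.** Same assumptions. The mean first-positive day is 0.1×3 + 0.1333×7 + 0.2667×15 + 0.5×30 = 20.23. For course length c, rate = 1,000 × 0.05 / (0.05×20.23 + 0.95×c):

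- c = 5: 50/5.76 = 8.7
- c = 7: 50/7.66 = 6.5
- c = 10: 50/10.51 = 4.8
- c = 14: 50/14.31 = 3.5

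Every group has the same 5% risk, yet the rate falls 8.7/3.5 = 2.5-fold.

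**4. Other course-length assumptions.** Simulation with lognormal (median 6, 8 or 10 days), exponential (mean 8) and uniform 1 to 21 day courses, 3% or 5% acquiring, and bands 1–3, 4–7, 8–15 and 16–30 days gave these highest-to-lowest ratios under no duration effect:

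- Exposure-length bands, acquisition on therapy only: 13 to 189. With two bands (lognormal median 8, 5%) the ratio was 4.7 to 6.3.
- Exposure-length bands, acquisition continuing to day 30: 1.9 to 43, sometimes U-shaped.
- Recorded course, counting as written: 5.4 to 9.

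**5. Does the remedy work?** Recorded course with on-therapy events and days only gives 5.0 against 5.0 in the setting of step 1. In the lognormal median-8, 5% setting, with on-therapy acquisition only, recorded course gives 5.4 / 5.3 / 5.2 / 5.2, and splitting each patient's antibiotic-days over time gives 5.2 / 5.3 / 5.2 / 5.2.

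Splitting is not enough if the clock is left as written. In the setting of step 2, with bands 1–3, 4–7, 8–15 and 16 or more days, it gives 5/3,000, 6.67/3,505, 13.33/2,017 and 25/375, that is 1.7 / 1.9 / 6.6 / 67 per 1,000.

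**The case against.** The strongest reply is that the article never says the duration result groups patients by the exposure length in Statistical analysis. That length is introduced for the overall incidence. The treatment data listed under Variables include duration of therapy, in the same words as the promised result. A reader might infer that the plan bands patients by the truncated length and that the duration comparison is therefore an artefact as it stands. **This objection stands against that reading**: no sentence makes the link. Nor does every grouping by final duration fail, since recorded course with matched on-therapy counting is flat. It is also incomplete to say that acquisition cuts exposure short, because a first positive after stopping lengthens it.

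Further points against:

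- *Size.* The 0 and 40 in step 2 follow from the assumed courses and the swab days. They show the mechanism and do not predict the trial's results. This stands.
- *Stakes.* The Outcomes section lists the rate overall, by class, by drug and by risk class, not by duration, and shorter courses are raised only as a hypothesis. This stands.
- *Detail for an analysis plan.* Band limits and model coding do belong there. But the end-dates for exposure are stated here, and step 3 shows that they distort the result even under the favourable reading. Silence about the grouping variable is not the whole issue.
- *Different cause.* The distortion in step 3 comes from mismatched numerator and denominator, not from outcome-dependent banding. That is true, and the remedy must therefore deal with both.

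**Conclusion.** The point holds in a conditional form. The grouping variable for the duration result is not named, and the one exposure length defined for analysis depends on the outcome. Banding by that length gives several-fold differences in most settings examined (as low as 1.9-fold in one) when duration has no effect. Banding by recorded course with the counting as written gives a false fall with longer courses: about 2.5-fold under one assumed mix, and 5.4- to 9-fold under the others tried.

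These sizes rest on assumed course lengths and bands, a constant or even acquisition rate, and course length independent of acquisition. The fall under recorded-course banding also needs acquisition to continue after treatment stops; if acquisition occurred only on therapy, that distortion would vanish. The documents do not support the stronger conclusion that the planned comparison is certain to be an artefact. What is affected is an expected output, not an outcome listed under Outcomes.

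**What to change.** State in Statistical analysis, and repeat under Implications of the hypothesis, that:

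1. the duration result will not band patients by the exposure length defined there;
2. each patient's follow-up is split by cumulative antibiotic-days already received, and each acquisition and each antibiotic-day goes to the band current at that time;
3. acquisitions and days are counted over the same period for acquirers and non-acquirers, for example on therapy plus one fixed post-therapy window for all. If a window is added, its days enter the denominator and the rate is labelled accordingly;
4. the Cox model carries cumulative antibiotic-days as a time-updated covariate.

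Because acquisition is seen only at swabs, bands ending on swab days are convenient, and a rule is needed for a positive whose swab interval spans the end of therapy.

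A simpler acceptable alternative is to group by recorded course length with the same matched period. It assumes that acquisition does not itself change the course length.

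Cost: analysis wording and slightly more programming on start, stop and swab dates already collected. No change to enrolment or sampling.
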